### Data analysis

2.5

We will perform a comprehensive analysis combining behavioral outcomes of CRS-R_index_ (R code available at)^2^ and neuroimaging data (fMRI, MRS, PET-CT). Statistical analyses will be conducted at both the individual and group levels, comparing outcomes before and after treatment, as well as between intervention and control groups. The main statistical approach will include repeated-measures ANOVA to examine within- and between-group effects, accounting for potential confounding variables. Continuous variables will be analyzed using paired or independent sample t-tests, while categorical variables will be assessed using the Mann–Whitney U test. Chi-square tests or Fisher’s exact tests will be employed to evaluate and document adverse events. To explore associations between neurotransmitter concentrations and other outcomes, regression analyses will be conducted. For SSEPs, changes in amplitude and latency before and after treatment will be compared using t-tests. EEG data will be analyzed using EEGLAB (41) to evaluate both local and cross-regional functional connectivity metrics, including phase locking value (PLV) and power spectral density (PSD). Functional MRI assessments will be conducted using SPM12 (36) to examine seed-to-seed functional and effective connectivity during both resting-state and task-based conditions. MRS will be primarily employed to compare pre- and post-treatment changes in Glx and GABA concentrations within the stimulated brain regions. Additionally, PET-CT imaging will be used to assess alterations in glucose metabolism, both in the stimulated areas and across the whole brain, following the intervention. For fMRI or EEG data analysis, we will implement FDR or FWER correction for multiple comparisons, but will not utilize machine learning validation approaches.

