## Abstract

**Background:**

Recent randomized controlled trials (RCTs) in patients with prolonged disorders of consciousness (pDoC) have yielded limited success. Among them, only studies involving amantadine have provided Class II evidence. The effects of other non-invasive brain stimulation techniques remain inconclusive, largely due to patient heterogeneity and the clinical complexities of implementing such interventions. Low-intensity focused ultrasound pulses (LIFUP), as a novel, non-invasive, and safe neuromodulation technique, have the potential to both stimulate and inhibit deep subcortical structures. This makes LIFUP a promising approach for modulating consciousness and promoting recovery in patients with pDoC. This study aims to evaluate the therapeutic efficacy and safety of LIFUP through a randomized controlled design.

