Based on the above, this study aims to evaluate the efficacy and safety of LIFUP as a potential neuromodulatory treatment. Another major focus of our investigation is to explore the relationship between multimodal neurofunctional assessments and behavioral outcomes in patients with pDoC. We hypothesize that participants receiving LIFUP delivered via either 100 Hz TUS or tbTUS will exhibit significantly improved behavioral recovery metrics compared to sham-controlled participants. Furthermore, we predict that 100 Hz TUS (19, 20) will induce superior neuroplastic effects relative to tbTUS (27), as quantified through multimodal functional connectivity analyses. These differential effects are anticipated to manifest as: (1) increased phase-locking value (PLV) in whole-scalp or region-specific high-density electroencephalography (HD-EEG), and (2) enhanced effective connectivity (EC) in task-based functional magnetic resonance imaging (fMRI), particularly within targeted neuromodulation networks.

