#### Sample size

2.2.3

For the behavioral assessment using the CRS-R, this study adopts a randomized controlled intervention design. Repeated measures will be analyzed using ANOVA to account for potential confounding variables. Based on a power analysis conducted using G*Power, with an effect size of 0.40, a significance level (*α*) of 0.05, statistical power (1 − *β*) of 0.80, a two-tailed test (α = 0.05), and an equal allocation ratio among the three groups (N1: N2: N3 = 1:1:1), the required each group sample size is calculated to be 18. After applying Bonferroni correction, the significance threshold for individual comparisons should be adjusted to α = 0.0167. To maintain this corrected alpha level, each group would require a sample size of 22. Considering a potential 15% dropout or exclusion rate, a minimum of 76 participants is required. Therefore, the study will enroll a total of 78 participants: 26 in Group A, 26 in Group B, and 26 in Group C. In the event of patient withdrawal or death during the study, we will implement standardized procedures. All withdrawal cases will be documented systematically, including: (1) voluntary withdrawal (participant-initiated consent revocation), (2) loss to follow-up (≥3 consecutive contact attempts failed), (3) clinical deterioration (≥2-point GCS decrease sustained for 48 h), and (4) investigator-determined withdrawal (with protocol-specified justification). For data management, all collected pre-withdrawal data will be retained per intention-to-treat principles, with final evaluable assessments carried forward for primary analysis. Mortality cases will trigger immediate reporting to the Ethics Committee of Shanghai Yangzhi Rehabilitation Hospital (Shanghai Sunshine Rehabilitation Center), followed by survival analysis using Kaplan–Meier methodology and independent adjudication of causes by a clinical endpoint committee. Statistical approaches will include sensitivity analyses (completers vs. non-completers) and multiple imputation for missing data.

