#### Randomization

2.2.4

Randomization will be performed using the random number generation function in the R programming language (set.seed). All eligible participants will be randomly assigned to one of three groups in a 1:1:1 ratio: Group A (100 Hz TUS), Group B (tbTUS), and Group C (sham stimulation). To ensure allocation concealment and fairness, a randomization sequence will be generated by an independent researcher who is not involved in the trial’s implementation or outcome evaluation. The randomization sequence will be kept confidential and will not be disclosed to outcome assessors or statisticians. Baseline assessments will be completed after group assignment. Healthcare providers and therapists involved in the participants’ care, including acupuncturists and cognitive therapists, will remain blinded to group allocation to minimize bias.

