The mechanism underlying recovery from pDoC remains poorly understood. At the level of neural functional connectivity, pDoC was associated with severe disruptions in resting-state network connectivity, particularly within higher-order networks (46). Interestingly, has been observed in the limbic system including the orbitofrontal cortex, insula, hypothalamus, and ventral tegmental area in patients with VS/UWS (47). Such hyperconnectivity may reflect early-stage injury responses, as brain injury often disrupted normal neural connectivity and may initially provoked compensatory overactivation (48). As described in studies of DBS, stimulation of the central thalamus could both increase and decrease functional connectivity, suggesting that the brain may adjust connectivity toward a balanced, homeostatic state during recovery (49). While tbTUS demonstrate excitatory (27) cortical effects, its deep nuclear actions appear more complex. Notably, recordings of local field potentials in the internal globus pallidus during intervention of 120 s tbTUS in DBS-implanted patients revealed enhanced theta and beta activity, though the underlying excitatory/inhibitory mechanisms remain to be elucidated (50). This temporal and spatial complexity suggests ultrasound’s therapeutic effects may vary by both disease stage and anatomical target. Finally, we suggest that the mechanisms underlying the recovery of DoC require more precise experimental designs of TUS. In the future, this approach could potentially be combined with DBS-implanted patients.

To our knowledge, this is the first randomized controlled trial to investigate the effects and safety of LIFUP on patients with pDoC. We aim to compare the effects of two different parameter sets (100 Hz TUS and tbTUS), and to explore the relationship between behavioral recovery in pDoC and BOLD and EEG signal changes, as well as thalamic concentrations of Glx/GABA. These findings may contribute to a better understanding of the neurobiological mechanisms underlying recovery in pDoC.

However, it should be noted that this is a single-center clinical trial. Future multicenter studies with larger sample sizes will be necessary to validate these results. Moreover, whether the optimal stimulation target should be the left thalamus or bilateral thalami remains an open question, requiring further clinical investigation.

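### Safety is a stated aim, but the only test named for adverse events is a chi-square or Fisher test at 26 per arm, which says little about harm; risks and risk differences with intervals should carry the evaluation

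*Protocol article*

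**What the plan says.** Safety appears as an aim in three places.

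- Abstract, Background: "This study aims to evaluate the therapeutic efficacy and safety of LIFUP through a randomized controlled design".
- Section 1 (Introduction): "this study aims to evaluate the efficacy and safety of LIFUP as a potential neuromodulatory treatment".
- Section 3 (Discussion), on the trial's novelty: "this is the first randomized controlled trial to investigate the effects and safety of LIFUP on patients with pDoC".

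Section 2.5 (Data analysis) names the method for adverse events: "Chi-square tests or Fisher’s exact tests will be employed to evaluate and document adverse events". It does not say which of the two tests applies when, at what significance level, or whether the comparison is three-way or pairwise.

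Section 2.2.3 (Sample size) works from the CRS-R only, "with an effect size of 0.40", and concludes that "the study will enroll a total of 78 participants: 26 in Group A, 26 in Group B, and 26 in Group C". Neither an adverse-event risk nor a relevant excess of harm enters that calculation.

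Harm is handled elsewhere too. Section 2.2.3 gives deaths a Kaplan-Meier analysis and independent adjudication of cause. Sections 2.1 and 2.3.6 provide for monitoring of vital signs and recording of adverse events.

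**The concern.** A significance test asks whether the data contradict equal risk. When the question is whether an intervention is safe, the reader needs to know how large an excess of harm remains compatible with the data, and a p-value does not say. In a small trial the two questions can have very different answers: the test is non-significant while the data still allow a large excess.

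Here the test is the stated means of evaluating adverse events, and the sample was sized for another endpoint. A likely report is that adverse events did not differ significantly between arms. Because the article presents the trial as the first randomised evidence on safety in this population, later trials could take that sentence as reassurance it cannot give.

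**Working it through.** **Inputs from the article.** 26 per arm, 1:1:1, with 22 evaluable per arm and 15% dropout (section 2.2.3). The tests are chi-square or Fisher (section 2.5).

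**Assumptions.** The article gives no adverse-event risk and no relevant excess, so sham risks of 5-30% and excesses of 10-30 percentage points are assumed. Two-sided 0.05 is also assumed, because none is stated for these tests; a stricter level could only raise the miss rates.

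**The plan's own figure.** 3 × 22 = 66 evaluable patients. 66 / (1 − 0.15) = 77.6, rounded up to 78, which is the enrolled number. (66 × 1.15 = 75.9, rounded up to 76, is the stated minimum.) So 78 is reproduced, from CRS-R inputs only.

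**Miss rates.** For true risks p0 (sham) and p1 (active), let X ~ Bin(26, p0) and Y ~ Bin(26, p1). The miss rate is 1 − Σ P(X = x) P(Y = y) over all pairs (x, y) for which the test gives p ≤ 0.05. It was computed by full enumeration.

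| Sham v active | Excess (points) | Fisher misses | Chi-square (uncorrected) misses |
|---|---|---|---|
| 5% v 15% | 10 | 92% | 78% |
| 10% v 20% | 10 | 91% | 82% |
| 5% v 20% | 15 | 78% | 60% |
| 10% v 25% | 15 | 81% | 69% |
| 5% v 25% | 20 | 60% | 43% |
| 10% v 30% | 20 | 68% | 53% |
| 20% v 40% | 20 | 75% | 63% |
| 30% v 50% | 20 | 77% | 68% |
| 5% v 30% | 25 | 42% | 27% |
| 10% v 35% | 25 | 53% | 38% |
| 10% v 40% | 30 | 38% | 25% |
| 20% v 50% | 30 | 46% | 35% |

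**Which column applies.** By the usual convention Fisher is used when an expected count falls below 5. At 5% v 20% the expected count per arm is 26 × 12.5% = 3.25, so Fisher. At 20% v 40% it is 26 × 30% = 7.8, so chi-square would ordinarily be used.

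**Pooling the active arms (52 v 26, Fisher).** Miss rates are 68% for 5% v 20%, 88% for 10% v 20%, 73% for 10% v 25% and 54% for 10% v 30%. Pooling helps but does not cure the problem.

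**What a p-value hides.**

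- No events in an arm: the upper limit of the two-sided exact 95% interval is 1 − 0.025^(1/n). For n = 26 this is 13.2%; for n = 52 it is 6.8%.
- 4 of 26 against 0 of 26: Fisher p = 0.11, while the Newcombe 95% interval for the risk difference runs up to about 34 points.
- 5 of 26 against 0 of 26: Fisher p = 0.051, uncorrected chi-square p = 0.019. The same data fall on opposite sides of 0.05 depending on which of the two named tests is used.

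**The case against.** Several points can fairly be made for the plan. Most of them limit what may be claimed.

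- **A reader might infer that the plan will treat a non-significant result as proof of safety.** The documents do not support that. No section states such a rule, a safety hypothesis or a margin. The Discussion asks for larger multicentre studies to validate the results and describes LIFUP used alone as still exploratory. The risk is one of misreading, not of a stated wrong decision.
- **A reader might infer that the test is the only safeguard or measure of harm.** It is not. Deaths have Kaplan-Meier analysis and adjudication, and vital signs are monitored. The accurate statement is that chi-square or Fisher is the only test named for adverse events.
- **A reader might infer that real harm would almost always be missed.** That is too general. The miss rate depends on risks the article does not give and on which test is used. An excess of 25 to 30 points is missed in only 25-53% of trials across the two tests.
- **Intervals may be in a full protocol or analysis plan that is not shown, and trials are commonly sized on the primary outcome.** Both are true. The absence of intervals from an article is no error, and neither is the sample size.

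What remains is a choice the article does make: it names a significance test as the way to evaluate adverse events under a headline aim. That choice is weak at this size, and the general call for larger studies does not say how the test results will be interpreted.

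**Conclusion.** The point holds as a weakness in a stated method, and section 2.5 should be changed. At 26 per arm, a chi-square or Fisher p-value for adverse events tells the reader little about safety. For the modest excesses that would still matter (10 to 15 points over a sham risk of 5-10%), the test misses more often than it detects: 78-92% with Fisher, 60-82% with chi-square. At 20 points, over sham risks of 5-30%, the ranges are 60-77% and 43-68%. These figures rest on assumed event risks, two-sided 0.05 and all 26 patients per arm contributing. With only 22 per arm the Fisher miss rates are much the same or slightly higher (80% for 5% v 20%, 72% for 10% v 30%). The 13.2% limit for zero events in 26 needs no assumed event risk.

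**What to change.** In section 2.5, make estimation the basis of the adverse-event evaluation:

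- For any adverse event, serious adverse events and death, report the risk in each arm with an exact (Clopper-Pearson) 95% interval.
- Report the risk difference with a 95% interval for each active arm against sham, and for both active arms pooled against sham.
- Keep the chi-square or Fisher p-values as descriptive.
- State that a non-significant result is not evidence of safety, and that the safety conclusion will be worded from the upper interval limits.

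The Kaplan-Meier analysis and adjudication of deaths can stay as they are. No new patients or data are needed. The cost is a few sentences, a few more table columns, and a more modest safety statement than a bare non-significant p-value would seem to allow.

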The mechanism underlying recovery from pDoC remains poorly understood. At the level of neural functional connectivity, pDoC was associated with severe disruptions in resting-state network connectivity, particularly within higher-order networks (46). Interestingly, has been observed in the limbic system including the orbitofrontal cortex, insula, hypothalamus, and ventral tegmental area in patients with VS/UWS (47). Such hyperconnectivity may reflect early-stage injury responses, as brain injury often disrupted normal neural connectivity and may initially provoked compensatory overactivation (48). As described in studies of DBS, stimulation of the central thalamus could both increase and decrease functional connectivity, suggesting that the brain may adjust connectivity toward a balanced, homeostatic state during recovery (49). While tbTUS demonstrate excitatory (27) cortical effects, its deep nuclear actions appear more complex. Notably, recordings of local field potentials in the internal globus pallidus during intervention of 120 s tbTUS in DBS-implanted patients revealed enhanced theta and beta activity, though the underlying excitatory/inhibitory mechanisms remain to be elucidated (50). This temporal and spatial complexity suggests ultrasound’s therapeutic effects may vary by both disease stage and anatomical target. Finally, we suggest that the mechanisms underlying the recovery of DoC require more precise experimental designs of TUS. In the future, this approach could potentially be combined with DBS-implanted patients.

To our knowledge, this is the first randomized controlled trial to investigate the effects and safety of LIFUP on patients with pDoC. We aim to compare the effects of two different parameter sets (100 Hz TUS and tbTUS), and to explore the relationship between behavioral recovery in pDoC and BOLD and EEG signal changes, as well as thalamic concentrations of Glx/GABA. These findings may contribute to a better understanding of the neurobiological mechanisms underlying recovery in pDoC.

However, it should be noted that this is a single-center clinical trial. Future multicenter studies with larger sample sizes will be necessary to validate these results. Moreover, whether the optimal stimulation target should be the left thalamus or bilateral thalami remains an open question, requiring further clinical investigation.
